## Abstract

**Background:**

A life threatening illness such as breast cancer can lead to a secondary diagnosis of PTSD (post traumatic stress disorder) with intrusive thoughts and avoidance as major symptoms. In a former study by the research group, 80% of the patients with breast cancer reported a high level of stress symptoms close to the diagnosis, such as intrusive thoughts and avoidance behavior. These symptoms remained high throughout the study. The present paper presents the design of a randomized study evaluating the effectiveness and cost-effectiveness of a stress management intervention using a stepped-care design.

**Method:**

Female patients over the age of 18, with a recent diagnosis of breast cancer and scheduled for adjuvant treatment in the form of chemotherapy, radiation therapy and/or hormonal therapy are eligible and will consecutively be included in the study. The study is a prospective longitudinal intervention study with a stepped-care approach, where patients will be randomised to one of two interventions in the final stage of treatment. The first step is a low intensity stress-management intervention that is given to all patients. Patients who do not respond to this level are thereafter given more intensive treatment at later steps in the program and will be randomized to more intensive stress-management intervention in a group setting or individually. The primary out-come is subjective distress (intrusion and avoidance) assessed by the Impact of Event Scale (IES). According to the power-analyses, 300 patients are planned to be included in the study and will be followed for one year. Other outcomes are anxiety, depression, quality of life, fatigue, stress in daily living and utilization of hospital services. This will be assessed with well-known psychometric tested questionnaires. Also, the cost-effectiveness of the intervention given in group or individually will be evaluated.

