### Design

The study is a prospective longitudinal intervention study with a stepped-care approach [13], where patients will be randomised to one of two interventions in the final stage of treatment. One of the key concepts in the stepped-care model is that the needs of the individual are matched to the appropriate level of care [13]. The first step is a low intensity intervention that is given to all patients. Patients who do not respond to this level are thereafter given more intensive treatment at later steps in the program. Since methods from CBT (cognitive behavior therapy) have already been shown not only to reduce the risk for PTSD [8] but also to have a positive effect on quality of life and psychological well being for patients with breast cancer [9,14], there is no control group in the study. All patients (n = 300) will receive the first level of the intervention program. All patients (estimated to n = 150) who continue to report stress symptoms after the first step of the intervention program will be given the chance to participate in the second step of the program. The second step includes randomisation to one of two treatments: a stress management group or individual stress management (See Figure 1). With this design it will be possible to study the prevalence of stress related symptoms as well as to study which factors predict which patients will be Clinically Significant Improved (CSI) with a basic level of education about stress management. In addition the study will help to identify those patients who need additional help and to compare the effects of individual and group interventions.

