		***Time of assessment***				
***Questionnaire***	**Inclusion**	*Intervention* *Step 1*	**3 months after inclusion**	*Interventions* *Step 2*	**1 month after completed intervention**	**12 months after completed intervention**
*n*	*300*	*300*	*300*	*150*	*150*	*300*
IES [15]	X		X		X	X
HADS [16]	X		X		X	X
EORTC QLQ C-30 [17]	X		X		X	X
EORTC QLQ BR-23 [18]	X		X		X	X
EQ-5D [19]	X		X		X	X
MFI [20,21]	X		X		X	X
Stress in daily living [22]	X		X		X	X
Self-reported sick leave and use of other professional services	X		X		X	X
Background data	X					X
Patient satisfaction with interventions [11]			X		X	X
PGPQ [23] (n = 150)			X		X	X

### Intervention, Step 2

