### Data analysis

SPSS® ANOVA will be used to analyze differences between groups and for repeated measures over time for the continuous variables while nominal (categorical) variables will be tested with chi square (exact). Although not all the criteria for normal distribution are met by this selection the parametric tests are robust enough to be used. Patients’ levels of stress related symptoms will be categorized according to recognized cut-off points (See references in Table 1). A hierarchical linear regression analysis will be used to examine which variables predict stress symptoms and utilization of health care services as well as sick leave and return to work. Power calculations have been done for IES based on data from Support Project. On the basis of these conditions (power = 0.8, p = .05 and effect size = 0.59) at least 64 patients must be included in each group (i.e. a total of 128) patients) to detect a significant difference on IES.

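### The primary outcome does not fix which IES score, which follow-up wave or which ANOVA effect decides the randomised comparison, so the false-positive risk is 5% to at most 18.5% depending on the reading

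*Protocol article*

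**What the plan says.** Four places in the protocol article bear on the primary comparison of group with individual stress management.

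- **Abstract, Method.** "The primary out-come is subjective distress (intrusion and avoidance) assessed by the Impact of Event Scale (IES"). Two components are named in brackets. No time point is given, and nothing says whether the components are summed or tested separately.
- **Design.** Randomisation takes place at Step 2, among "All patients (estimated to n = 150) who continue to report stress symptoms after the first step of the intervention program". The randomised comparison therefore starts after the 3-month assessment.
- **Table 1.** The IES is collected at inclusion, at 3 months, and at two points after randomisation: "1 month after completed intervention" and "12 months after completed intervention". Neither is marked as primary.
- **Data analysis.** ANOVA is planned for between-group differences and for repeated measures over time, with no effect singled out. The sizing reads "Power calculations have been done for IES based on data from Support Project", with "power = 0.8, p = .05 and effect size = 0.59", concluding that "at least 64 patients must be included in each group" "to detect a significant difference on IES". That describes one difference at one significance level.

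**The concern.** The sizing statement presumes one test. The outcome definition, the assessment schedule and the planned analysis together leave three choices open: the score (total, or intrusion and avoidance separately), the wave (1 or 12 months) and the effect (group, or group by time). Even with a single IES score, a repeated-measures ANOVA produces both a group test and a group-by-time test.

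If these choices are made after the data are seen, a favourable result on one component or at one wave could be presented as the primary result, and 5% would no longer describe the risk of a false claim. The choice also changes what the trial asserts: a benefit one month after the programme and a benefit a year later are different claims, and a group-by-time effect answers a different question from a group effect.

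**Working it through.** **Inputs from the article.** Significance level .05, power 0.8, effect size 0.59 and 64 per group (Data analysis); two named components (abstract); two IES waves after randomisation (Table 1).

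**Assumptions.** Tests are two-sided, since sidedness is not stated. Correlations between the test statistics are not given, so a range of 0 to 0.8 is shown.

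**1. The plan's own figure.** For two means, n per group = 2(z₀.₉₇₅ + z₀.₈)²/d².

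- With d = 0.59: 2 × (1.960 + 0.842)²/0.59² = 45.1, so 46 (47 with the t distribution). The stated 64 is not reproduced.
- With d = 0.50: 62.8, so 63 (64 with the t distribution), which matches.

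This mismatch is a separate point. It matters here only because the sizing is for a single test at .05, and because it affects the cost of a multiplicity correction (step 4).

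**2. Number of candidate tests.**

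- One score, one group effect: 1 test.
- One score at two waves, or two components at one wave, or one score with both the group and the group-by-time effect: 2 tests.
- Two components at two waves: 2 × 2 = 4 tests.

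Per-wave tests and a repeated-measures model are alternative analyses, so the group-by-time test is not added on top of the four.

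**3. Chance of at least one false positive when each test is at .05 and any success counts.** Under independence this is 1 − 0.95^k: for k = 2, 9.75%; for k = 4, 18.5%. For correlated tests, it is the probability that at least one of k equally correlated standard normal statistics exceeds 1.96 in absolute value:

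| Correlation (assumed) | 2 tests | 4 tests |
|---|---|---|
| 0 | 9.75% | 18.5% |
| 0.5 | 9.1% | 15.6% |
| 0.6 | 8.8% | 14.4% |
| 0.7 | 8.4% | 13.0% |
| 0.8 | 7.8% | 11.4% |

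Letting component and wave correlations differ does not change the picture. A simulation with separate component and wave correlations gives 16.1% when both are 0.5, 13.7% when both are 0.7 and 12.0% when both are 0.8. The ceiling relative to 5% is 18.5/5 = 3.7 times; the floor is 1.

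**4. Cost of keeping four primary tests under Bonferroni.** Each test is then at .05/4 = .0125. With d = 0.59 and 80% power, the requirement is 64.1, so 65 per group (66 with the t distribution). At 64 per group, power per test is about 79% if the effect is 0.59 but about 62% if it is 0.50.

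**The case against.** The strongest reply is that the article names one outcome, in the singular, and that the bracket merely describes what the IES measures. The scale has one row in Table 1 and is treated as one measure in the definition of clinically significant improvement and in the sizing. A repeated-measures ANOVA can take both waves into one model. On that reading there is one test and the error rate is 5%. This stands as a legitimate reading, and it is why the range starts at 5%.

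A reader might infer more: that the plan, followed as written, makes every component at every wave a primary test and so carries two to four times the stated error rate. The article does not support that. It never says the subscales will be tested separately or each wave on its own, or that success on any one test counts. Four times is not reached even under independence, which is implausible for repeated scores on one scale in the same patients.

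It can also be said that a journal article leaves the ranking of tests and multiplicity rules to a full protocol or analysis plan. That is fair for the details of the analysis, and the lack of a multiplicity rule alone would not be a finding. But the article does define its primary outcome, does size the trial on it and does describe the analysis, and those three statements together do not identify one comparison. Even the single-score reading leaves the group and group-by-time effects unranked.

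**Conclusion.** The point holds as an ambiguity, not as a demonstrated inflation of error. The article sizes the trial for one IES difference at .05 but does not identify which difference. Depending on the reading, the chance of at least one false-positive primary result is 5% (one score, one test), about 8 to 10% (two tests), about 11 to 16% (four tests at correlations of 0.8 down to 0.5), or at most 18.5% (four independent tests). The figures above 5% rest on two assumptions that the article does not state: that each test is run unadjusted at two-sided .05, and that any success would be reported as the primary result. The correlations are also assumed. It should be settled before the data are analysed, because afterwards the choice could follow the results.

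**What to change.** State one primary score, for example the IES total, and one primary contrast: group versus individual stress management at a single named wave, for example 12 months after the intervention ends. Analyse it by ANCOVA adjusted for the 3-month IES, which is measured before randomisation and already collected, and test it once at two-sided .05. Declare the subscales, the other wave and the group-by-time test secondary. Which wave should be primary is for the investigators to decide; nothing in the article settles it.

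If both subscales or both waves are to remain primary, state a multiplicity rule and check the sample size against it, given the loss of power shown above if the effect is nearer 0.50.

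The change takes one or two sentences and needs no extra patients or data collection, and the covariate should improve precision. The price is giving up a primary claim on the other wave or on a single subscale.

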**Discussion:**

This randomized clinical trial will provide additional empirical evidence regarding the effectiveness of a stress-management program given in group or individually during adjuvant therapy in terms of decreased stress, minimizing fatigue, and maintaining or enhancing patients’ quality of life and psychological well-being.

**Trial registration:**

ClinicalTrials.gov Identifier: NCT01555645

## Background

A life threatening illness such as breast cancer can lead to a secondary diagnosis of PTSD (post traumatic stress disorder) [1]. The reported frequency of PTSD for breast cancer patients varies between 2–22%, depending on methods of measurement. At present it is therefore difficult to draw any conclusions about the actual prevalence of PTSD. Intrusive thoughts, avoidance behavior and worry are all common symptoms. Nordin and Glimelius [2] reported that clinical levels of worry or depression in combination with intrusive thoughts in individuals with breast cancer make it possible to identify women who will need psychological support at a later stage of treatment. In a study [3] it was found that measures of avoidance behavior could predict the effects of treatment on an individual’s quality of life. Extensive avoidance behavior at the start of treatment is correlated with deterioration in physical and social functioning as well as impaired general health. Half of the women diagnosed with breast cancer in Sweden are under the age of 65 and at least theoretically gainfully employed [4]. To juggle the demands of work and a family, especially when there are children living at home, is a demanding task [5]. To be diagnosed with breast cancer on top of these demands can be the straw that breaks the camel’s back. At present there is very little research that has examined this combination of stress factors in women diagnosed with breast cancer.

In an international perspective there is a fair amount of evidence which indicates that methods which are based on cognitive behavior therapy can improve health-related quality of life (HRQoL), reduce psychosocial stress and increase perceived Personal control of treatment side-effects and disease symptoms for cancer patients [6,7]. According to SBU (The Swedish Council on Technology Assessment in Health Care) providing cognitive behavior therapy 1–3 months after a traumatic event reduces the occurrence of PTSD in states of intensive stress [8]. At present there is a lack of solid research findings for comparisons of cost-effectiveness and outcome [8].

The research group “Support project” has studied the effect of individual counselling conducted by a specially trained nurse [9]. This intervention was compared to the results of therapy conducted by a psychologist and to a group that received treatment as usual. The project started in 1997 with special training for nurses [10]. The project continued during for the next 5 years and data collection was concluded in January 2002. Patients in this study had been diagnosed with breast cancer and were offered adjuvant treatment. A total of 179 patients were consecutively included. The results showed that both active treatments had a positive effect, measured in terms of increased HRQoL and decreased symptoms of stress (e.g. intrusive thoughts) in comparison to the control group who received treatment as usual [9]. More patients in the control group took advantage of the psychosocial support that was available for all patients in standard care as compared to both intervention groups. The level of satisfaction was generally high in both intervention groups [11]. However patients in the nurse-counselor groups reported that greater satisfaction with interventions for worry, information about their illness, prognosis, tests, treatment as well as general contact with health care facilities than patients in the psychologist groups. Utilization of health care and number of days on sick leave can be attributed to the adjuvant treatment [12]. Both the intervention groups had lower total costs for medical care than the control group who required more days for in-patient care. The conclusions that can be drawn from this study are that the psychosocial interventions were useful for breast cancer patients, that they were relatively inexpensive and that interventions offered by nurses were as effective as those given by psychologists. The results of the “Support Project” described above generated additional questions. Most patients reported relatively high levels of HRQoL as well as relatively low levels of symptoms and side-effects of their illness and treatment. Despite these findings 75% of the patients reported that they had problems for which the psychosocial interventions provided help. A more detailed analysis of the data showed that 80% of the patients in the study reported a high level of stress symptoms initially, such as intrusive thoughts and avoidance behavior. These symptoms remained high throughout the study. Other symptoms such as worry and depression were also reported at high levels initially but these symptoms had decreased to normal levels after 3 months. This indicates that here is a need for closer examination of other factors for breast cancer patients, such as stress-related symptoms and behavior, predictors for stress, effects on role and social functions as well as utilization of heath care, sick leave and return to work settings. In addition there is a need to study how psychosocial interventions with a focus on stress management can influence the above-mentioned factors.

This paper presents the design of a randomized multi-centre trial to evaluate the effectiveness and cost-effectiveness of a stress management intervention using a stepped- care approach. The first step is a low intensity intervention that is given to all patients. Patients who do not respond to this level are thereafter given more intensive treatment at step 2 in the program. They will in step 2 be randomised to more intensive stress-management intervention in a group setting or individual. The hypothesis is that half of the individuals assigned to a low intensity intervention will be significantly improved after treatment. For individuals who continue to have symptoms after low intensity treatment it is hypothesized that continued treatment in a group setting with high intensity interventions will be more cost-effective. In addition the assumption is that reduction of stress symptoms in women with breast cancer will lead to a reduction in socio-economic costs.

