## Methods

### Patients

Female patients over the age of 18, with a recent diagnosis of breast cancer and scheduled for adjuvant treatment in the form of chemotherapy, radiation therapy and/or hormonal therapy are eligible for this study and will consecutively be included in the project. Patients will be recruited from three hospitals in the central part of Sweden (Uppsala, Gävle and Falun). Criteria for exclusion are an ongoing psychiatric condition or language deficiencies in Swedish. According to the power calculations, a total sample of 300 patients is necessary.

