### Data collection

Data will be collected by use of well-known questionnaires. An outline of the assessment points and questionnaires are included in Table 1. When patients are included in the study, they were mailed the baseline questionnaires, which included a signed consent to participate and a prepaid envelope. Later measurements will be sent out to the patients’ homes, together with a stamped, pre-addressed envelope. Patients who have not returned the completed questionnaires after 14 days will be contacted by telephone by a member of the project staff to insure as high a response rate as possible. Information about the patients’ demographic and medical background will be obtained from their medical records. Utilization of hospital services will be collected from the hospitals’ computer systems. Information about utilization of other professional care facilities will be collected from patients’ self-reports. Sick-leave information will also be collected by self-report. The nurse-counsellor will record attendance at individual and group sessions.

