## Discussion

The interventions that are planned for in this project are directed towards symptoms that can make or break the course of illness for an individual patient. Hopefully the project will show that a stepped-care approach can help and support individual patients at the right level of care. All patients will receive stress management training. Those who require more help will receive additional treatment for their symptoms in the form of individual or group counselling. Health care and society may gain substantially from the planned intervention program, both in the form of individualized psychosocial support and reduced utilization of health care, preserved work capacity or a quicker return to work. The more intensive support will only be offered to those patients who show a clear need. For research purposes it is also important to increase what is known about stressors that are specific to women diagnosed with breast cancer and to develop interventions that are directed at these symptoms. This study will be conducted in three different counties in central Sweden which contributes to increased generalization and dissemination of the results of the study. This can lead to implementation of similar evidenced-based psychosocial care for cancer patients within a large geographical area.

Limitations of the study should be noted as well. The lack of a true control-group in step-2 can result in difficulties to interpret the effects of the stress-intervention. If there is a positive result, we cannot be absolutely sure that this effect would not be present in an untreated group. However, we consider not to have a untreated control since methods from CBT (cognitive behavior therapy) have already been shown not only to reduce the risk for PTSD [8] but also to have a positive effect on quality of life and psychological well being for patients with breast cancer [9,14]. It would not be ethical to withdraw patients in need from a treatment that has been found effective.

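### The stated analyses of service use, sick leave and cost do not adjust for adjuvant treatment type, and the stress-to-cost assumption lies outside what is randomised

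*Protocol article*

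**What the plan says.** All of this is in the protocol article.

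- **Background, on this trial:** the cost idea is worded as an assumption, namely that "reduction of stress symptoms in women with breast cancer will lead to a reduction in socio-economic costs". The cost hypothesis proper is that group format will be more cost-effective in step 2. The Discussion names the hoped-for gains: "reduced utilization of health care, preserved work capacity or a quicker return to work".
- **Background, on the earlier study by the same group:** "Utilization of health care and number of days on sick leave can be attributed to the adjuvant treatment [12". The next sentence adds: "Both the intervention groups had lower total costs for medical care than the control group who required more days for in-patient care".
- **Methods, Patients:** women are eligible if "scheduled for adjuvant treatment in the form of chemotherapy, radiation therapy and/or hormonal therapy", so the treatment mix is wide.
- **Methods, Design:** there is no untreated control. Everyone receives step 1. Only those who still report symptoms and wish to continue are randomised, to group or individual format.
- **Methods, Data collection:** hospital service use comes from the hospitals' systems, sick leave from self-report, and medical background from the records.
- **Methods, Data analysis:** ANOVA is used for group differences and for change over time in continuous variables. A hierarchical linear regression examines which variables "predict stress symptoms and utilization of health care services as well as sick leave and return to work". No covariate or predictor is named.

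**The concern.** The protocol itself identifies a strong determinant of service use and sick leave, recruits patients who differ widely on it, and then states an analysis that does not use it. The consequences differ between the two kinds of comparison.

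**Randomised comparison (group versus individual).** Allocation does not depend on treatment type, so leaving it out does not shift the estimate systematically. The unexplained variance does widen the confidence interval for utilization, sick leave and cost, and one arm may by chance contain more intensively treated women.

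**Non-randomised comparisons (stress-cost association, change over time).** Recruitment happens around the appointment at which adjuvant treatment is discussed, and follow-up runs to 12 months after the intervention. Service use is therefore observed during treatment and after it. With no untreated control, a fall in use may be the end of treatment. If treatment type is related to stress as well as to cost, a stress-cost association may reflect treatment alone.

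At stake is whether a statement that reducing stress reduces societal cost could be supported by these data.

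**Working it through.** The plan gives no figure for cost, utilization or sick leave, so there is none to reproduce for this point. The only computable figure is the IES sample size of 64 per group. It does not follow from the stated effect size of 0.59 (a two-sided calculation gives 46 to 47 per group). That is a separate matter; 64 is used below only as an arm size.

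**1. Chance imbalance between randomised arms.** Inputs: n = 64 per arm (Data analysis); share on chemotherapy 0.5 (assumed).

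SD of the difference in shares = √(2 × 0.5 × 0.5 / 64) = √0.0078 = 0.088. The 95% range is ±1.96 × 0.088 = ±0.173, about ±17 percentage points.

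With 75 per arm (half of the 150 expected in step 2 under Design): √(0.5 / 75) = 0.082, and ±1.96 × 0.082 = ±0.16.

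The unadjusted standard error already reflects this variation. It is lost precision, not bias.

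**2. What adjustment would gain in the randomised comparison.** If treatment type explains a fraction R² of the outcome variance, the standard error is multiplied by √(1 − R²), which is equivalent to 1/(1 − R²) times the patients. The R² values are assumed.

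| R² | SE ratio | Reduction in SE | Equivalent sample size |
|---|---|---|---|
| 0.20 | √0.80 = 0.89 | 11% | 1.25× |
| 0.30 | √0.70 = 0.84 | 16% | 1.43× |
| 0.50 | √0.50 = 0.71 | 29% | 2.0× |

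**3. Confounding of a stress-cost association.** Assumed model: n = 300, half on the more intensive treatment. Treatment shifts stress by a and cost by b, in units of the within-treatment SD. Stress has no effect on cost. The expected unadjusted slope of cost on stress is

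0.25ab / (1 + 0.25a²).

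For a = 0.6 and b = 1.0 this is 0.15 / 1.09 = 0.138. A simulation of 2,000 trials per row gave:

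| a | b | Mean slope, treatment omitted | False-positive rate | Mean slope, treatment included |
|---|---|---|---|---|
| 0 | 0.5 | 0.000 | 5.0% | about 0 |
| 0 | 1.0 | 0.002 | 4.5% | about 0 |
| 0.3 | 0.5 | 0.036 | 9.1% | about 0 |
| 0.3 | 1.0 | 0.073 | 20.6% | about 0 |
| 0.6 | 0.5 | 0.070 | 24.2% | about 0 |
| 0.6 | 1.0 | 0.137 | 60.2% | about 0 |

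In the same runs an unadjusted comparison of two randomised arms of 64 had a false-positive rate of 4.8% to 6.4%, close to the nominal 5%.

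So the randomised contrast is valid but less precise than it could be. The association is biased only if treatment type also relates to stress, and entering treatment type removes that bias under this model.

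**The case against.** A reader might infer more than the documents support.

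- **That the earlier study contradicts the cost assumption.** It does not. The sentence after the attribution to adjuvant treatment reports lower medical costs in both intervention groups than in the control group. Treatment can determine the level of use while an intervention changes part of it. That evidence, however, came from a comparison with usual care, which this trial does not have.
- **That treatment will drive these outcomes and be read as an effect of stress.** This is too certain. The Background says intrusion and avoidance, the primary outcome, stayed high throughout the earlier study; only worry and depression returned to normal, after 3 months. No text links treatment type to stress, and without that link the association across treatment types is unbiased (rows with a = 0). Data analysis does not name stress as a predictor of cost. The Discussion already concedes, in general terms, that a positive result might also occur without treatment, though it mentions neither costs nor adjuvant therapy.
- **That the plan has decided to ignore treatment type.** This cannot be known. An article may leave its predictor list to a fuller plan, and a missing list is not itself an error.

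It is also fair to object that the sizes are generic: any prognostic covariate yields the same formulas.

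What stands after this: the analysis method is stated (ANOVA between groups), the determinant is named by the authors themselves, and the causal cost assumption concerns a contrast that the trial does not randomise.

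**Conclusion.** The point holds in a limited form. For the randomised group-versus-individual comparison, omitting treatment type costs precision and leaves chance imbalance (about ±17 points at 64 per arm), with no systematic bias. Adjustment would be worth 1.25 to 2 times the patients if treatment type explains 20% to 50% of the variance. For any non-randomised stress-cost association or fall in costs over time, the course of treatment may confound the result. With no true effect of stress, the false-positive rate would be 9% to 60% if treatment shifts stress by 0.3 to 0.6 SD and cost by 0.5 to 1.0 SD, and about 5% if it does not shift stress.

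The chemotherapy share, the R² values and the shifts are all assumptions; the article supplies none of them. The assumption that lower stress lowers societal cost is not refuted by the earlier study. This trial cannot test it by randomisation.

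**What to change.** 1. In the utilization, sick-leave and cost analyses, adjust the group-versus-individual comparison for the adjuvant treatment type planned at inclusion. Eligibility requires that treatment be scheduled, so the type should be available then or from the medical records.
2. Enter the same variable as the first block of the hierarchical regression for utilization, sick leave and return to work.
3. Report any stress-cost relation, and any fall in costs over time, as association only. Limit causal cost statements to the randomised group-versus-individual contrast.
4. Do not adjust the arm comparison for treatment status observed after randomisation, since that may introduce bias.
5. If wanted, separate scheduled adjuvant care from other hospital use in a sensitivity analysis. Making this the main cost outcome would be a debatable choice of costing perspective, and the article does not show that the hospital systems can make the split.

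Items 1 to 4 need no extra patients or visits. They cost a small amount of additional analysis and a narrower socio-economic claim. Item 5 would also need hospital contacts to be coded.
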